#### Psychotherapy dose and duration

The psychotherapy in all three arms (ST, CBT, IST) is offered in accordance with a guideline-adherent psychiatric-psychotherapeutic hospital care for depression [101] as a combined concept including two group- (100 min. each) and two individual sessions (50 min. each) per week applied over the course of 7 weeks. The group-sessions are offered in a “semi-open” manner in order to keep the maximal group size stable (eight participants). That is, newly randomized participants are integrated in the ongoing group-session circle by the beginning of a treatment week. The received amount of treatment sessions of each participant is documented, so it can function as a control variable in the statistical analysis, since it might differ from the protocol guidelines for various reasons. Six and 24 months after study completion, participants are invited to a follow-up measurement appointment and are offered an additional individual psychotherapy session after the measurements have been taken.

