#### Individual supportive therapy

IST can be considered as an active and nonspecific, non-ST and non-CBT approach. Following the concept of a bio-psycho-social disease model of MDD, IST is based on the common factors of psychotherapy, which include among others support of the patient, therapeutic alliance, activation of resources, actualization of the patient’s problems, motivational clarification, and problem solving [95, 96]. These factors can be fostered from the therapist side through techniques like being supportive, applying an understanding and acknowledging conversational style, calming assertions, putting the focus on perceiving progress, or using interested inquiries. The IST manual is based on three pillars: the patients’ personal resources, the therapeutic alliance between him/her and the therapist, and the focus on emotions. Regarding the latter, patients are encouraged and supported to give space to emotions, whenever they are experienced during the psychotherapy session. This happens without IST being based on a psychodynamic frame work such affect phobia treatment [97] or emotions being the foundational and central subject matter of the treatment like in emotion-focused therapy [98].

Therapists are instructed to apply a supportive, non-judgmental, open, empathic, tolerating, positive communication style. The IST-program uses the insights of client-centered communication skills. Patients define the topics and content of each session by themselves. The therapists are instructed not to use specific psychotherapeutic intervention strategies from ST or CBT. Similar concepts of supportive therapy have been used elsewhere [99] as an active control arm that takes into account these important carriers of interpersonal medicine in general and have been shown to be effective in the treatment of MDD.

In order to avoid and control for different expectancy effects between treatment arms, therapists in the IST condition are encouraged to introduce participants into the concept and common factors of IST. Additionally, therapy expectations are assessed using Patient Questionnaire on Therapy Expectation and Evaluation [100] and considered in statistical analysis.

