### Concomitant care

In order to protect against biases, all study participants are asked not to join any other psychotherapeutic program such as mindfulness training. Potential influencing factors that form part of an inpatient/day clinic treatment program such as Sports therapy, case management, or ergotherapy are documented for later use in the statistical analysis as potential confounder.

The OPTIMA study design does not regulate parallel psychopharmacotherapy but leaves the decisions hereon to the psychiatrist in charge. The psychopharmacological substances a patient receives throughout the intervention phase, however, is documented in terms of type and dosage.

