### Power and statistical analysis

Power estimation for the current investigation is based on the main research question on the effectiveness of ST and hypothesis H1 on the superiority of ST over IST regarding the primary outcome (BDI-II). We presume that the minimal clinically important difference (MCID) regarding BDI-II scores should be related to initial depression severity and a patient perspective of perceived improvement [188]. Button and colleagues estimated a minimum reduction of 17.5% of BDI-II scores as MCID. Based on our baseline pilot data, an effect size of d = 0.4 would allow us to detect all outcome differences that can be considered as MCID in our target sample which consists of moderate to severe depressed patients in an inpatient and day clinic setting. If setting power to 0.80 and *α* to 0.05 while using two-sided t-tests and following a 1:1:1 randomization to ST, CBT, or IST, it is necessary to recruit *n* = 99.1 per group resulting in an overall sample size of *N* = 300 (rounded) participants to identify differences in BDI of d = 0.4.

Regarding H2 on the non-inferiority of ST compared with CBT, a sample size of *n* = 100 per group, a one-sided significance level of α = 0.05, and setting power to 0.80 will allow us to evaluate a non-inferiority margin of d = .36. This is even lower than what can be considered as MCID [188] and takes into account the potential role of concurrent medication during the psychotherapy treatment.

We will apply different methods such as Holm procedure [189] in a scientifically appropriate manner regarding all future data analyses derived from the current study in order to prevent family wise error rate. The Holm method can be applied in same cases like Bonferroni correction to control for multiple testing, but is a more advanced and powerful tool [190].

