Nevertheless, this study faces some challenges and has methodological limitations. First, it is in the nature of psychotherapy trials, that the blinding of participants and personnel (except from raters) is impossible to achieve. Thus, therapy expectancy effects constitute a potential risk of bias [200]. Second, the study duration of 7 weeks could be judged as too short to capture lasting treatment effects of psychotherapy. Specifically, one might expect a greater impact of psychotherapy when it is administered for a longer period of time. Yet, considering the inpatient and day clinic sample of the trial, 7 weeks displays a realistic picture of the clinical reality rather than a longer stay at the hospital. To account for the short treatment phase, we plan two later assessments at 6 and 24 months post-treatment to cover these long-term effects. Third, from a pure methodological perspective, a “psychopharmacotherapy only” and/or a “psychopharmacotherapy free” treatment arm would enable us to detect the relative contributions of ST and ADM to the recovery more accurately. However, the combination of ADM and psychotherapy is considered as gold standard in the treatment guidelines of MDD [93]. Given that the participants in our sample suffer from rather severe forms of MDD at the time point when they are being enrolled in the study, we decided not to include a “psychotherapy only” or “psychopharmacotherapy only” arm in the study design for ethical reasons. Fourth, the semi-open structure of the group sessions means varying patient constellations and potential therapist change, which might disrupt therapy processes and the development of therapy alliance and group cohesion. Fifth, the measures in the current research are time consuming and demanding. Loss of motivation is a core feature of depression and therefore, the study procedures might bias the selection of participants and facilitate drop outs. Even though, we cannot totally rule out this limitation, we hope to lower such biases by reducing the obligatory measurements to a minimum and adapting measurement procedures to the participants’ schedule to make participation as convenient as possible. Beyond that, we will use CONSORT guidelines [201] to ensure a transparent reporting of the trial and detect and evaluate potential remaining sampling biases when interpreting results in terms of generalizability. Since the major parts of the measurements happen before and after treatment, we do not consider them to interfere with the process of psychotherapy. Sixth, psychotherapy is one element of comprehensive inpatient and day clinic treatment approach including ADM and further elements of psychiatric care. Nevertheless, as outlined above, we assume psychotherapy and specific intervention techniques like in ST to play a major role in the treatment of depression and therefore expect an additional effect to non-specific therapy (IST). In accordance with treatment guidelines [101] and to assure psychotherapy not to be neglected in the overall care, we choose a relatively high treatment dose when comparing ST with CBT. In order to avoid biases in favor a non-inferiority hypothesis, we chose a rather small non-inferiority margin and will take this aspect into account when interpreting the results. Furthermore, all additional therapies and ADM will be documented and considered for later use in the statistical analysis as potential confounder. Even though we assume the further elements of psychiatric care to average out between arms, improvement in symptom severity cannot be directly associated to the specific psychotherapy interventions alone. The inclusion of psychotherapy in daily psychiatric care constitutes a methodological challenge, but simultaneously provides the opportunity to test treatment effects in a realistic scenario. Finally, pilot data suggests that the application of the mentioned inclusion and exclusion criteria will result in a sample consisting of partly moderate, but mainly severe forms of MDD. Such a sample represents reality in an inpatient and day clinical settings, but has to be taken into account as a factor when generalizing the results.

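### The protocol gives variables that arise after randomisation the role of control variable or confounder, which leaves open an adjustment that could bias the H1 and H2 contrasts

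*Protocol article*

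**What the plan says.** Four places in the protocol article give such variables a role in the analysis.

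- *Psychotherapy dose and duration*, on sessions: "The received amount of treatment sessions of each participant is documented, so it can function as a control variable in the statistical analysis".
- *Concomitant care*, on sports therapy, case management and ergotherapy: these "are documented for later use in the statistical analysis as potential confounder". The same section says that medication is recorded over the intervention phase and left to the treating psychiatrist.
- *Discussion*, sixth limitation: "all additional therapies and ADM will be documented and considered for later use in the statistical analysis as potential confounder". This follows directly on the expected advantage over IST (H1), the comparison with CBT and the choice of non-inferiority margin (H2).
- *Individual supportive therapy*: "therapy expectations are assessed using Patient Questionnaire on Therapy Expectation and Evaluation [100] and considered in statistical analysis". The stated aim is to control for expectancy differences between arms.

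*Power and statistical analysis* names linear mixed-effect models for the outcomes, under intention-to-treat with multiple imputation. It does not say which kinds of covariate may enter.

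**The concern.** A confounder of a treatment comparison must influence which treatment is assigned. Under 1:1:1 randomisation, nothing that happens after allocation can do so. Sessions attended, co-therapies used and medication given over the 7 weeks can be consequences of the arm, of the patient's prognosis, or of both. Conditioning on a consequence of arm removes any part of the effect that runs through it. Where the variable shares causes with outcome, conditioning also opens a non-causal path. All randomised patients may still be in the model, but its arm coefficient no longer estimates the effect of assignment.

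Two of these variables have another role in the protocol itself. Missing more than six sessions is one definition of drop-out (*Inclusion and exclusion criteria*), and the drop-out rate is a secondary outcome. The expectation questionnaire is listed under H5 among the common factors through which the arms are expected to work (*Further measures of potential MOCs for process comparison*). A post-allocation score cannot be both adjusted away and studied as a mechanism of the same effect.

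At stake is a spurious or diluted difference for H1, and a wrongly granted or wrongly refused non-inferiority claim for H2.

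**Working it through.** **1. The plan's own figures.** The inputs from *Power and statistical analysis* are "If setting power to 0.80", α set "to 0.05 while using two-sided t-tests", "following a 1:1:1 randomization to ST, CBT, or IST", and "participants to identify differences in BDI of d = 0.4".

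- H1, normal approximation: n = 2(1.960 + 0.842)²/0.4² = 2 × 7.85/0.16 = 98.1 per group. The t-test solution is 99.08, so the stated 99.1 reproduces, and 3 × 99.1 = 297.3, rounded to 300. Power at 100 per group is 0.804.
- H2, one-sided α = 0.05, power 0.80, n = 100: detectable margin = (1.645 + 0.842) × √(2/100) = 2.487 × 0.1414 = 0.352. The stated 0.36 has power 0.816.

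These figures do not depend on covariate adjustment and are not in dispute. They supply the yardsticks: 0.40 for H1 and 0.36 for H2.

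**2. Formula.** Let M be a post-randomisation variable in SD units. Let a be the effect of arm on M, b the effect of M on benefit, and g and h the loadings of a common cause (prognosis) on M and on benefit. In a linear model:

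adjusted arm effect = total effect − a × (b + g × h)

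The term a × b is effect removed; a × g × h is the path opened. If a = 0, the shift is zero. The documents give none of a, b, g or h, so every value below is assumed.

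**3. Sessions, no true difference.** Take b = 0 and g = h = r, so the session–outcome correlation is r² in size and the shift is a × r². Simulation: 5,000 trials per setting, 100 per arm, least squares of outcome on arm and sessions.

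| a (SD) | r² | a × r² | Simulated shift | Type I error |
|---|---|---|---|---|
| 0.3 | 0.25 | 0.075 | 0.074 | 8.0% |
| 0.5 | 0.25 | 0.125 | 0.125 | 14.9% |
| 0.3 | 0.49 | 0.147 | 0.148 | 20.8% |
| 0.5 | 0.49 | 0.245 | 0.244 | 47.5% |

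A separate run of 4,000 trials gave shifts of 0.076, 0.123, 0.149 and 0.245 SD, and type I errors of 8.6, 13.5, 21 and 48%. Here the arm with more sessions is made to look worse.

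**4. Direction.** Milder setting: |a| = 0.2, b = 0, g × h = 0.25, shift 0.2 × 0.25 = 0.05. Stronger setting: |a| = 0.4, b = 0.3, g × h = 0.25, shift 0.4 × 0.55 = 0.22. The standard error is held at 0.1414, so any change in residual variance from adding M is ignored.

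| Truth | Effect of ST on M | Adjusted effect | Consequence |
|---|---|---|---|
| H1, d = 0.40 | raised | 0.35 to 0.18 | power falls from 0.81 to 0.70, then 0.25 |
| H1, d = 0.40 | lowered | 0.45 to 0.62 | effect overstated |
| H2, d = −0.36 | lowered | −0.31 to −0.14 | false non-inferiority 0.10 to 0.46 instead of 0.05 |
| H2, d = −0.36 | raised | −0.41 to −0.58 | false non-inferiority 0.023 to 0.001 |

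For example, at −0.14: Φ((0.36 − 0.14)/0.1414 − 1.645) = Φ(−0.089) = 0.46.

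**The case against.** The strongest reply is that the protocol never says it will do this. The wording is permissive throughout, and no sentence puts any of these variables into the H1 or H2 model. The analysis in this trial also covers the process hypotheses H3 to H5 and exploratory prediction, where dose and medication can properly appear. What is fixed for the arm comparison, intention-to-treat and sizing by plain t-tests, points away from such adjustment. A full covariate list may stand in an analysis plan that is not shown. A reader might infer that the primary analysis will adjust for these variables and that H1 and H2 are therefore biased; the document supports neither step.

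Two further replies also stand. The timing of the expectation questionnaire is in an appendix that is not shown. Allocation is concealed from patients until the day of the first session, so a T0 score would be a legitimate covariate. The numerical inputs have no source in the protocol either: all arms have the same session schedule, and the *Discussion* expects other elements of care to balance across arms.

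The stated role itself remains. Calling in-trial sessions, co-therapies and medication control variables or confounders is wrong for the arm comparison, whatever a later plan lists. The *Discussion* sentence sits among the safeguards for H1 and H2, and the expectation sentence refers to differences between arms. If other care does balance, no adjustment is needed to remove an imbalance; if arm shifts it, adjustment can bias.

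**Conclusion.** The point holds as a wrongly stated role that invites an invalid adjustment, not as a committed error in the primary analysis. Bias needs two conditions that the document does not establish: the variable enters the H1 or H2 model, and arm affects it. If both hold, the shift can go either way. Its size is unknown; the range of about 0.07 to 0.24 SD, with type I error of about 8 to 48%, illustrates assumed arm differences of 0.3 to 0.5 SD in sessions and assumed correlations of 0.25 to 0.49. It comes from a single-time-point linear model for sessions only, not from the planned mixed model. For expectations, the concern applies only to scores taken after allocation. The sample-size figures are unaffected.

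It is still worth correcting before analysis. Patients and therapists are not blinded, the primary outcome is self-reported, and an optional set of post-allocation covariates leaves room to choose the model after seeing results.

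**What to change.** State that the primary H1 and H2 models adjust only for variables measured before allocation: T0 BDI-II, treatment unit (the stratification factor) and, where recorded before allocation, T0 medication and T0 therapy expectation.

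In *Psychotherapy dose and duration*, *Concomitant care*, *Individual supportive therapy* and the *Discussion*, withdraw the control or confounder role, as regards the arm comparison, from sessions received, in-trial co-therapies, in-trial medication and post-allocation expectation. Report these by arm, and use them only in supplementary mediation, dose-response or process analyses labelled as such.

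The cost is wording: no extra patients and no change to the sample size. The article describes medication records for the intervention phase only, so T0 medication can be used only if a separate record from before allocation exists; the rule works without it.

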### Blinding

Clinical interviews and ratings are conducted by raters, trained in workshops and individual sessions, evaluated and supervised, who are blind to the psychotherapy arm [103]. In case of an unblinding of a rater, corresponding ratings are conducted by another member of the rating team, thus assuring blinding throughout the sample. Interrater reliability between raters is assessed intermittently based on the ratings of the same patient by all raters. After evaluation, an additional training is offered as needed.

### Concomitant care

In order to protect against biases, all study participants are asked not to join any other psychotherapeutic program such as mindfulness training. Potential influencing factors that form part of an inpatient/day clinic treatment program such as Sports therapy, case management, or ergotherapy are documented for later use in the statistical analysis as potential confounder.

The OPTIMA study design does not regulate parallel psychopharmacotherapy but leaves the decisions hereon to the psychiatrist in charge. The psychopharmacological substances a patient receives throughout the intervention phase, however, is documented in terms of type and dosage.

## Measures and hypotheses

### Primary and secondary measures for outcome comparison

We choose BDI-II [87] as primary outcome to capture the change of symptom severity over the course of 7 weeks. BDI-II represents a widely used and well established self-assessment of MDD [104, 105] and thus assures comparability of results with former research. In order to overcome some of BDI-II related restrictions such as sensitivity to maladaptive personality traits [106], we added MADRS [88], as clinical assessment of change in MDD as secondary outcome. Further secondary outcomes are recovery rate (change in diagnosis) measured by the Munich-Composite International Diagnostic Interview (M-CIDI) [107], change in general psychopathology using the Brief Symptom Inventory (BSI) [108], change in global functioning and quality of life according to the World Health Organization Disability Assessment Schedule (WHODAS) [109] and the World Health Organization Quality Of Life (WHO-QOL) assessment [110]. Further secondary outcome measures are drop-out rates, and remission rates. Based on previous research, our main hypotheses are that ST including its intervention techniques is more effective (superior) in the treatment of MDD compared to IST as a nonspecific-common factor psychotherapy [111] (H1), and 2) ST is non-inferior compared with CBT regarding treatment response and recovery rates operationalized by primary and secondary outcomes after the intervention and after 6 months [24] (H2).

### Further measures of potential MOCs for process comparison

In order to delineate the MOCs of ST and compare them with underlying mechanisms of CBT and IST, we include multiple potential mediators, most of them measured in weekly intervals (cf. [62]). Depending on treatment condition, we hypothesize different MOCs to be relevant.

In accordance with the theoretical concept of ST, we consider schemas (Young Schema Questionnaire – Short Version 3) [112], Young Positive Schema Questionnaire) [113], modes (Schema Mode Inventory) [114], therapeutic alliance (Working Alliance Inventory) [65, 112], attachment style (Relationship Scales Questionnaire) [115], affect (Need for Affect Questionnaire [116], the Positive and Negative Affect Schedule) [117, 118], and emotion regulation (Emotion Regulation Questionnaire) [119, 120] to function as MOCs of ST regarding the change in MDD (H3).

Based on previous research [62] and in contrast to ST, for CBT we assume cognition related aspects of depression (Automatic Thought Questionnaire [121], Dysfunctional Attitude Scale [122], Cognitive Style Questionnaire – Short Form in German [123], Internal and External Control Beliefs Scale [124], and self-efficacy measured by *Allgemeine Selbstwirksamkeitsskala* [125]) to mediate change in MDD (H4).

Additionally, we expect all three conditions, but especially the non-specific treatment arm (IST) to work through common factors of psychotherapy, such as goal setting (Goal Attainment Scale) [126], therapy expectations (Patient Questionnaire on Therapy Expectation and Evaluation) [100], further general mechanisms (Scale for the Multiperspective Assessment of General Change Mechanisms in Psychotherapy) [127], and non-specific session characteristics (Session Evaluation Questionnaire) [128] to be associated with change (H5).

In order to examine temporal and causal relations between MOCs and outcomes measures, measurements should happen at the same time point [55, 56]. We therefore include outcome measures (BDI-II, BSI) and MDD related constructs such as thought-action fusion in the context of suicidality [129], resilience (Brief Resilience Scale) [130], perceived stress (Perceived Stress Scale) [131, 132], and coping with depressive symptoms (Response Style Questionnaire) [133] on a weekly base. See Additional file 1: Appendix A for details regarding time points of measurement.

Beyond that, the exploration of potential MOCs of ST should not be restricted to weekly self-reports, but also include information from other sources in order to get a more comprehensive understanding of the course and processes during psychiatric care [62]. Therefore, we complement the set of weekly self-report variables by adding actimetry measures to assess locomotor activity, psychophysiological measures during the actual psychotherapy session, and continuous measures of depression-related parameters such as mood and repetitive negative thinking:

